### Data Collection

#### Overview

We set pre- and postimplementation data collection periods to extend for 6 months each, based on the staggered dates when the ICU e-transfer tool was implemented at each hospital. Patients transferred from the ICU prior to the intervention implementation date of their hospital are considered in the preimplementation period, while patients transferred from the ICU on or after the intervention implementation date of their hospital are considered in the postimplementation period.

Data collection involves (1) electronic extraction from provincial system repositories and a local critical care database, (2) manual abstraction from the patient’s electronic and paper medical record by trained researchers, and (3) manual rating of sampled transfer summaries by clinicians. Survey data of ICU clinician perspectives was collected pre- and postimplementation of the e-transfer tool. The flow of data collection is shown in Figure 2. Where feasible, we are deidentifying hospital name, dates, and clinician and patient identifiers from clinical documents (eg, transfer summaries and clinician progress notes) secured for manual data abstraction. All data will be encrypted and retained in a secured office.

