## Methods

### Setting

This evaluation study takes place in four acute care hospitals servicing a single city, Calgary, Alberta, Canada, which has a referral population of approximately 1.7 million. Three of the four hospitals are academic hospitals operating a combined 56 adult medical-surgical ICU beds; the fourth is a nonacademic, community-based hospital operating 10 ICU beds. The annual ICU admission rate across the city approximates 3000 patients. In addition to the CIS hosting the e-transfer tool (ie, Sunrise Clinical Manager), all ICUs also use a dedicated provincial critical care CIS (ie, eCritical MetaVision) and clinical analytics system (ie, eCritical TRACER) that capture key demographic, clinical, health care service, and outcome data for all ICU patients [49]. ICUs are staffed by multidisciplinary teams; those in academic-based hospitals operate with a clinical fellow and 4 to 10 residents working under the supervision of an attending physician. One ICU has an NP. Critical care resident rotation blocks are 4 weeks in duration. The community-based ICU functions with an attending physician and 4 NPs.

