### E-Transfer Tool Implementation

The e-transfer tool has been sequentially implemented into the four study hospitals at a new site every 2 months. This occurred between July 2018 and January 2019. The study biostatistician (AS), who was not involved with clinical practice in the ICUs, randomized the order of hospitals for implementation. Dictation remained available after implementation, but the ICU e-transfer tool was endorsed as the primary method to prepare ICU transfer summaries; as well, use of the tool was supported with strategies that have been successfully used in previous local initiatives, including in-person and web-based education, point-of-care support, and electronic audit and feedback [50].

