### Participants

ICU patients from the four participating hospitals were eligible for inclusion in the study if the patient (1) was admitted to the ICU during the defined pre-post periods; (2) was 18 years of age or older; (3) had an ICU stay equal to, or longer than, 24 hours; and (4) was transferred from the ICU to an in-hospital PCU. Patient admission lists were extracted retrospectively by a data analyst with the critical care CIS repository (ie, eCritical TRACER). As the primary creators of most ICU transfer summaries [42], NPs and residents were invited to participate in a brief survey soliciting their experience creating transfer summaries.

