#### Sample Size Calculations

Sample size calculations were based on the cluster-specific pre-post study design. Based on our pilot [41,42], we calculated a required sample size of 144 pre- and 144 postimplementation ICU transfer summaries from each hospital to assess our primary outcome. This will be sufficient to detect an absolute difference in our primary outcome of 15% for each hospital with 82% power and an α value of 5% based on a baseline proportion of 20%; we observed a change in our pilot from 23% to 83%. A random sample of 24 ICU patients per hospital per month, over 6 months pre- and 6 months postimplementation, will facilitate secondary analyses, which accommodate the possibility of secular trends. The study biostatistician (AS) determined the random sample by assigning computer-generated random numbers to the complete list of patients transferred from each ICU within the study period, which was extracted by a data analyst with the critical care analytics system (see Figure 2). The study biostatistician was blinded to the method used to create the summary at the time of randomization.

To collect clinician ratings of the transfer summary quality, we calculated requiring 64 summaries preimplementation (ie, 16 per hospital × 4 hospitals = 64) and 64 summaries postimplementation (ie, 16 per hospital × 4 hospitals = 64), which will be sampled from aforementioned summaries, to detect an absolute difference in means as small as 0.5, assuming an SD of 1, with 80% power and an α value of 5%. The same patient cases will be used to assess for suspected post-ICU adverse events.

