#### Data Analysis

Demographic characteristics pre- and postimplementation for each hospital will be described using medians with IQRs, means with SDs, and frequencies with percentages, as appropriate. The primary outcome will be compared within each hospital pre- and postimplementation using separate logistic regression models for each hospital, with adjustment for the following patient characteristics: age, sex, reason for ICU admission, status on ICU admission (ie, Charlson Comorbidity Index, APACHE II, GCS, and SOFA), therapies received while in ICU (ie, ventilation, vasoactive medications, intermittent hemodialysis, and continuous renal replacement therapy), status on transfer (ie, transfer delay time, transfer decision cancellations, and ICU occupancy), and ICU length of stay. Pooled analyses across all four hospitals will use mixed-effects logistic regression models with a fixed effect for intervention and a fixed effect for time in months, in order to model the underlying secular trend. A fixed effect for patient characteristics will also be used, as noted above, and random effects will be used for hospital and hospital by time to account for intracluster and interperiod correlation. In case of poor model fit or convergence issues due to a limited number of clusters, hospital-level analyses will be considered by aggregating the primary outcome over all summaries in each hospital during each month and using linear regression of the aggregated cluster-period proportions of complete and timely summaries with fixed effects for hospital and time in months. Secondary outcomes will be analyzed as described for the primary outcome, using within-hospital and pooled analyses. Wilcoxon rank-sum tests will be used to compare ICU and hospital length of stay, and log-rank tests will be used to compare time from ICU discharge to hospital mortality.

Open-ended comments collected through clinician surveys will be analyzed according to standard practices of qualitative textual analysis.

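### The pooled model's single intervention term draws mostly on the first two months after go-live, so it estimates the 6-month average effect only if the effect is immediate and constant

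*Protocol article*

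**What the plan says.** Under Data Collection (Overview), the post period opens on the go-live date with no transition window: "patients transferred from the ICU on or after the intervention implementation date of their hospital are considered in the postimplementation period". The windows are equal: "We set pre- and postimplementation data collection periods to extend for 6 months each". The tool was "sequentially implemented into the four study hospitals at a new site every 2 months", and sampling is even over time: "A random sample of 24 ICU patients per hospital per month, over 6 months pre- and 6 months postimplementation".

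Data Analysis makes the within-hospital comparison the primary one, using a separate logistic model for each hospital. The pooled analysis uses "mixed-effects logistic regression models with a fixed effect for intervention and a fixed effect for time in months", with random effects for hospital and hospital by time. If that model fits poorly or fails to converge, the fallback is a linear regression of hospital-month proportions with hospital and month fixed effects. Neither pooled model lets the effect vary with time since go-live.

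Some statements make gradual uptake plausible. Dictation stayed available, and use was built up through "in-person and web-based education, point-of-care support, and electronic audit and feedback". Setting adds: "Critical care resident rotation blocks are 4 weeks in duration".

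**The concern.** A single on/off term in a staggered design does not weight the post months equally. Once calendar time is in the model, the term is informed mainly by months in which some hospitals have switched and others have not. Here those months are concentrated soon after each go-live. If the tool takes time to be adopted, the pooled estimate leans on its weakest weeks and can make an effective tool look weak. If use fades as support ends, the estimate leans on the strongest weeks and overstates what was achieved over six months. The pooled model is the analysis with a stated secular-trend term, and the same approach is applied to secondary outcomes, so readers are likely to rely on it.

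**Working it through.** **The plan's own figure.** With 144 pre and 144 post summaries per hospital (24 × 6), 20% against 35% and two-sided 5%, the normal-approximation power is 81.7%. The stated 82% is reproduced.

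**Design.** From the article: 4 hospitals, go-live at months 0, 2, 4 and 6, a 6+6-month window each, and 24 summaries per hospital-month, giving 48 hospital-months. Of the 24 post hospital-months, those with another hospital still in its control period number 6 for the first hospital, 4 for the second, 2 for the third and 0 for the fourth. By month since go-live, months 1-2 supply 6 of these 12, months 3-4 supply 4, and months 5-6 supply 2.

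**Weights.** The intervention coefficient is a row of (X'V⁻¹X)⁻¹X'V⁻¹ applied to the hospital-month means. Summing that row by month since go-live gives, for months 1 to 6:

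- fallback model (hospital and categorical month effects): 0.55, 0.55, 0.15, 0.15, -0.20, -0.20
- hospital effects with linear time: 0.60, 0.42, 0.25, 0.08, -0.09, -0.26
- random hospital and hospital-by-month effects: months 1-2 together carry 0.73 to 1.06; month 6 is always negative and month 5 nearly always

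The article gives no intracluster correlation. I assumed 0.01 to 0.10, with the between-month correlation within a hospital 0.5 to 1 times the within-month value. Whether time is linear or categorical is not stated, so both were run. Shortening the first hospital's pre window by one month barely changes the fixed-effect results.

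**Effect of assumed uptake curves.** The expected estimate is the sum of weight × effect in that month. In the fallback model:

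- no effect in month 1, then full: 1 - 0.55 = 0.45
- half effect in month 1: 1 - 0.5 × 0.55 = 0.73
- fading use (100, 100, 100, 80, 60, 40%): 1 - 0.2 × 0.15 + 0.4 × 0.20 + 0.6 × 0.20 = 1.17

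As fractions of the full effect, on the risk-difference scale:

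| Assumed effect by month | True 6-month average | Fallback model | All pooled models |
|---|---|---|---|
| Immediate, constant | 1.00 | 1.00 | 1.00 |
| 80%, then full | 0.97 | 0.89 | 0.88-0.92 |
| 50%, then full | 0.92 | 0.73 | 0.70-0.81 |
| 0, then full | 0.83 | 0.45 | 0.40-0.62 |
| 1/3, 2/3, then full | 0.83 | 0.45 | 0.45-0.62 |
| Fading use | 0.80 | 1.17 | 1.00-1.18 |

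On the log-odds scale with hospital fixed effects, the 0-then-full curve gives 0.41 to 0.47 of the full log odds ratio for 20% to 35%, and 0.31 to 0.38 for the pilot's 23% to 83%.

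**Within-hospital comparison.** With no time term stated and equal monthly samples, each post month has weight 1/6, so the expected risk difference is the 6-month average. In the 0-then-full case that is 5/6 = 0.83 of full effect. The post proportion is then 0.20 + 0.15 × 0.83 = 0.325, and per-hospital power is 68% instead of 82%.

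**The case against.** The strongest reply has four parts.

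- The pooled model is secondary. The primary comparison and the sample size rest on within-hospital contrasts, which weight the months equally. This stands. A reader might infer that the trial's main result could be halved; the article does not support that.
- No uptake curve is given, and education, point-of-care support and endorsement of the tool as the main method all argue against a month of zero effect. This stands too. The weights follow from the design, but any figure for bias needs an assumed curve.
- Counting from go-live is a legitimate choice for a study of implementation. This stands. Removing start-up weeks from the main estimate would change the question and, under slow uptake, would favour the tool.
- Two facts in the article look like evidence of a start-up problem but carry little weight. Eligibility requires that a patient "had an ICU stay equal to, or longer than, 24 hours", so eligible patients leaving on go-live day were admitted before the tool was live. That is guaranteed for only about the first day of a 6-month window, and the primary outcome concerns the summary at transfer. Four-week resident blocks bring new users throughout all six months, and the community ICU is described with an attending physician and nurse practitioners only, so one rotation is not a transition length the article establishes.

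What the reply does not answer is that the pooled coefficient fails to estimate the 6-month average that the go-live definition implies, unless the effect is immediate and constant. The bias is also not reliably conservative, as the fading case shows. Recording the preparation method for each transferred patient will reveal slow or fading uptake, but it does not alter what the coefficient estimates.

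**Conclusion.** The point holds for the secondary pooled model and its fallback. Between 0.73 and 1.10 of the single term's weight falls on the first two post months, across the assumed correlations and both codings of time. It would be too strong to say that the pooled estimate will be about half the true effect. That needs a first month with no effect, or a ramp of about two months; at 80% effect in month 1 the estimate is about 0.9, and with an immediate effect there is no bias. It would also be too strong to call the go-live definition wrong or the primary comparison distorted, since that comparison is only diluted to the 6-month average. The calculations ignore patient-level covariates and, apart from the log-odds check, use the risk-difference scale. This is a worthwhile, inexpensive improvement and not a flaw in the primary analysis.

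**What to change.** Keep the go-live definition and the within-hospital primary comparison. For the pooled analysis, prespecify a model with a separate effect for each month since go-live, and report the average of those six effects beside the single-term estimate. Add sensitivity analyses, pooled and within-hospital, that separate or omit the first month after go-live.

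The first-month indicator should not replace the monthly average. Under the 1/3, 2/3, full ramp it still gives only 0.75 to 0.85 of full effect. Under fading use it gives about 0.95 to 1.16, against a true average over months 2 to 6 of (1 + 1 + 0.8 + 0.6 + 0.4)/5 = 0.76.

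The cost is analysis wording only, because 24 summaries per hospital per month are already sampled. The standard error of the 6-month average rises by about 12% to 41% over the single-term estimate, depending on the intracluster correlation and time coding. A separate month-1 term raises it by about 11% to 18%. With four hospitals the monthly model may itself have convergence problems, so the linear fallback should carry the same month-since-go-live terms. Outcome abstraction was still under way when the article was written, so on that timetable the change could be fixed before results are known.

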**Figure 2 figure2:**
[figure not shown]
Data collection flow. B: critical care Code Blue database (data source); CIS: clinical information system; E: electronic extraction by CIS analyst (data collection method); ICU: intensive care unit; LOS: length of stay; M: manual extraction by study researcher (data collection method); P: paper chart (ie, medical doctor or nurse practitioner daily progress notes; data source); S: Hospital CIS (ie, Sunrise Clinical Manager; data source); T: critical care CIS analytics (ie, eCritical TRACER; data source).

#### Patient Demographics

Patient demographic data includes the following: age; sex; ICU and hospital admission and discharge dates, times, and locations; hospital mortality; comorbidities; ICU interventions (ie, intubation, ventilation, vasoactive medications, and dialysis); and severity of illness measures, including the Acute Physiology and Chronic Health Evaluation II (APACHE II) score [51], the Glasgow Coma Scale (GCS) score [52], and the Sequential Organ Failure Assessment (SOFA) score [53].

#### Outcome Measures

##### Overview

The primary outcome of interest is a binary composite measure of two conditions: information presence and availability (see Table 1). In the first condition, the presence of four essential information elements in the transfer summary—goals of care designation, diagnosis, list of active issues on transfer, and medications to continue on transfer—will be assessed and recorded as *yes* or *no*. All four elements must be present to be recorded as *yes*. In the second condition, the availability of the transfer summary to the accepting clinicians at the time of patient transfer from the ICU will be recorded as *yes* or *no*. Transfer summaries that meet these two conditions will be coded as *present*; those that do not will be coded as *absent*.

Secondary outcomes of interest fall into three main domains (see Table 1): (1) transfer summary quality (ie, completeness, timeliness, and clinician ratings), (2) patient outcomes (ie, post-ICU rapid response activation, cardiac arrest, adverse events, and ICU readmission), and (3) clinician perceptions. The rate of use of the e-transfer tool will also be measured by extracting the type of method—dictation or tool—used to prepare the medical summary for each patient transferred from the ICU during the study period.

**Table 1 table1:** Evaluation outcome measures.

Domain and outcome		Outcome description
Primary outcome—binary (present or absent) composite measure of two conditions: information presence and availability (both conditions need to be met)		Presence of four essential information elements: Goals of care Diagnosis Problem issues on transfer Medications to continue on transfer Completed transfer summary available to patient care unit (PCU) at the time of patient’s transfer out of the intensive care unit (ICU)
**Transfer summary quality**		
	Overall completeness: proportion of eight requisite information elements present in transfer summary (%) and presence or absence of each essential information element in transfer summary	Summative score of the presence (score=1) of eight essential information elements—the four elements listed above and the following elements: Patient medical history Patient supportive needs (ie, venous thromboembolism prophylaxis, isolation, mobility, or nutrition) Patient attachments (ie, lines and tubes) Medication reconciliation
	Timeliness: availability of summary relative to the date and time of patient transfer (in hours)	Difference between the following: Date and time transfer summary was transcribed (ie, dictated summaries) or last edited (ie, electronic summaries) and Date and time of patient transfer from ICU
	Clinician ratings: clinician ratings of perceived general quality of transfer summary (median, IQR)	Rate five criteria on a 7-point Likert scale: Organization Completeness Pertinence Overall satisfaction Confidence that accepting team will understand patient care plan
**Patient outcomes**		
	Occurrence of negative patient outcomes within 3 days post–ICU transfer (%)	Patient events occurring within 3 days post-ICU: ICU readmission Adverse events Rapid response team activation Cardiac arrest
	Hospital and ICU total length of stay (in days)	Time between admission and discharge
	Mortality (in hours)	Time from ICU transfer to hospital mortality
ICU clinicians’ perceptions of their last transfer summary		Rate seven criteria on a 7-point Likert scale: Process: understood process to produce high-quality summary Workload: manageable to complete within routine ICU workflow Effectiveness: format able to communicate all relevant information clearly and logically Revisions: able to revise as new information becomes available Timely: able to complete at the time of patient transfer from ICU Satisfaction: produced a high-quality summary Confident that receiving PCU team will understand the patient care plan Length of time required to complete last transfer summary, including gathering all relevant information

##### Transfer Summary Quality

###### Completeness of Information

Trained researchers will manually abstract overall completeness of information in the summary. Completeness will be calculated as the sum of the individual binary scores (1=present; 0=absent) that the researchers will record for eight prospectively identified information elements prioritized as requisite from a list of 63 essential elements identified as important in ICU transfer summaries [43]. The eight information elements are as follows: goals of care designation, patient medical history, diagnosis, ICU active problem list, patient supportive care needs, patient attachments (ie, lines and tubes), active medications, and medication reconciliation. We designed a chart review form in REDCap (Research Electronic Data Capture) [54] (see Multimedia Appendix 1). As the researchers will need to access relevant clinical documents in study patients’ medical records, they will not be blinded to the study period or hospital.

###### Timeliness of Information

Timeliness of the summary is defined as the difference in hours between the date and time the patient transferred out of the ICU and the date and time the transfer summary was either transcribed, in the case of dictated documents, or last updated in the CIS, in the case of e-transfer tool documents.

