### Local Initiative to Standardize Transfer Summaries: The Electronic ICU Transfer Tool

In 2017, we began designing an evidence-informed, computer-enabled, ICU-specific communication tool in the primary, integrated patient care CIS—Sunrise Clinical Manager (Eclipsys Corporation)—used in four acute care hospitals in a single Canadian city. This work was initiated as a quality improvement project to improve upon the conventional system of dictation that physicians and NPs—herein called ICU clinicians—use to prepare medical transfer summaries for ICU patients [41]. To dictate a summary, ICU clinicians use eScription, 2010 release (Nuance Communications), a health information management dictation, speech recognition, and transcription (DST) platform. The clinician verbalizes relevant patient transfer information to create a voice file that is run through speech recognition software to create a text report. The report is then edited by a transcriptionist and sent to the designated ICU clinician for approval before being uploaded for electronic viewing in the CIS as well as to a provincial, web-based health data repository accessible by community-based physicians (Alberta Netcare).

The content and structure of the ICU electronic transfer (e-transfer) tool was based on a national survey of existing transfer summary tools [42], subsequent consensus-based recommendations of two independent multidisciplinary groups of health care providers [41,43], and a heuristic evaluation [41]. The e-transfer tool consists of 10 overarching document sections: visit data, goals of care, allergy and intolerances, diagnoses and visit issues, course in ICU, investigations, medications, discharge to home or community, send copies to, and completion. These sections are designed with a user interface combination of structured fields (eg, checkboxes); automated fields, which pull in relevant patient data from other CIS locations; and free-text fields (see Figure 1). The tool permits ICU clinicians to open an ICU summary as a clinical document directly in the patient’s EMR and edit the summary over the course of the patient’s ICU stay. As with the DST system, the designated ICU clinician must approve transfer summaries. The summaries remain in the CIS and are uploaded to the provincial repository.

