**Figure 1 figure1:**
[figure not shown]
Electronic transfer tool sections and screenshots. ICU: intensive care unit.

In a small pilot test of the e-transfer tool in one ICU [42], electronic summaries had a significantly greater proportion of essential information fields completed overall (median 87.5%) than those prepared by dictation (median 62.5%) and were available to receiving teams closer to patient release (2.3 versus 45.0 hours). Primary users of the e-transfer tool also responded positively to its use, establishing favorable evidence to scale up implementation across additional municipal hospitals.

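### Timeliness is clocked at transcription for dictated summaries and at last edit for tool summaries, so it is measured differently largely by period; the primary outcome is affected if its availability condition uses the same timestamps

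*Protocol article*

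**What the plan says.** Timeliness in hours is a secondary outcome. Under Timeliness of Information, the summary's time is when it was "either transcribed, in the case of dictated documents, or last updated in the CIS, in the case of e-transfer tool documents", compared with the time the patient left the ICU. Table 1 gives the same rule: "Date and time transfer summary was transcribed (ie, dictated summaries) or last edited (ie, electronic summaries".

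The section on the local initiative describes both workflows. A dictated report is edited by a transcriptionist and then "sent to the designated ICU clinician for approval before being uploaded for electronic viewing in the CIS". A tool summary is opened in the patient's electronic record and can be edited throughout the ICU stay. It also needs approval by the designated clinician.

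The second condition of the primary composite is "the availability of the transfer summary to the accepting clinicians at the time of patient transfer from the ICU", recorded as yes or no (Outcome Measures, Overview). Table 1 adds that the summary must be a completed one. Neither place names the timestamp that decides the answer.

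**The concern.** A pre-post comparison of timing needs the same event timed in both periods. Here the event changes with the method of preparation, and the method changes largely with the period: the control condition is dictation alone, and after implementation the tool is the recommended method (E-Transfer Tool Implementation). Dictation stayed available, so the overlap between method and period is large but not complete.

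The planned analysis cannot remove an error of this kind. Adjustment for patient characteristics and a monthly time trend (Data Analysis) does not touch a measurement difference that switches on with the intervention. At stake is the timeliness comparison and, if the primary's availability condition comes from the same timestamps, one of the two conditions of the primary outcome.

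**Working it through.** **1. Where each clock stops in its workflow** (Local Initiative section; Timeliness of Information; Table 1)

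- Dictation: voice file, speech recognition, transcriptionist edit, clinician approval, upload and viewing. The clock stops at transcription, before the last two steps.
- Tool: document opened in the record, edits during the stay, clinician approval. The clock stops at the last edit, wherever that falls relative to approval or to the first usable version.
- Common to both: approval by the designated clinician. A shared event exists.

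**2. Direction of the error in hours**

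Let *a* ≥ 0 be the mean time from transcription to viewable for dictation, *e* the mean of (last edit minus first viewable) for the tool, and *u* the share of post-period summaries made with the tool. Assume all pre-period summaries are dictated and *a* is the same in both periods.

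- Recorded pre mean = true pre mean − *a*
- Recorded post mean = true post mean + *u·e* − (1 − *u*)·*a*
- Recorded improvement (pre − post) = true improvement − *a* − *u·e* + (1 − *u*)·*a* = true improvement − *u*(*a* + *e*)

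The recorded improvement is too small whenever *a* + *e* > 0. It is too large only if the last edit precedes viewability (for example, because approval came later) by more than *a* on average. The documents give none of *a*, *e* or *u*.

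**3. Does the clock reach the primary outcome?**

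For: Table 1 labels the secondary measure "Timeliness: availability of summary relative to the date and time of patient transfer (in hours", and the Abstract calls the primary a composite of timeliness and completeness. Against: the primary is a separate yes/no item, and no sentence derives it from these timestamps. The link is plausible but not stated.

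**4. The plan's own power figure** (Sample Size Calculations: 144 per period per hospital, 20% against 35%, α 5%)

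Power = Φ{[|d| − 1.96·√(2p̄(1−p̄)/n)] / √([p₁(1−p₁) + p₂(1−p₂)]/n)}

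With p̄ = 0.275: (0.15 − 1.96 × 0.05262) / 0.05188 = 0.903, so power = 81.7%. The stated 82% reproduces (two-sided).

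**5. Illustration if the primary does use these clocks** (assumed error rates; all post summaries made with the tool)

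Tool clock late: a share *m* of summaries that truly meet the composite (35%) is scored absent, so p₂ = 0.35(1 − *m*).

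| *m* | p₂ | Difference (points) | Power |
|---|---|---|---|
| 5% | 33.25% | 13.25 | 72.3% |
| 10% | 31.5% | 11.5 | 60.8% |
| 20% | 28.0% | 8.0 | 35.5% |
| 30% | 24.5% | 4.5 | 14.8% |

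Dictation clock early: if 5% to 30% of the pre summaries scored present (20%) were not yet viewable, the true pre rate is 0.20 × 0.95 = 19% down to 0.20 × 0.70 = 14%. The true difference is then 16 to 21 points where 15 is recorded.

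Reverse case: if the clocks favoured the tool by 2, 5 or 10 points with no true effect (20% in both periods), the chance of a significant result in the tool's favour would be 6.1%, 17.2% or 50.0% per hospital, against a nominal 2.5%.

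**The case against.** The quoted rule defines a secondary outcome, and the primary's availability item may be scored in another way. The abstraction form (Multimedia Appendix 1) is not shown, and an article may leave item-level coding to it. This stands: the point cannot assert that the primary is mis-clocked, nor treat the lack of a coding rule in the article as a fault in itself.

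Last edit is also defensible for a document that keeps changing. Table 1 asks for a completed summary, and the last edit is the cautious time at which the scored content is known to exist. This stands in part. It explains the tool clock, but it does not make that clock comparable with a dictation clock that stops before approval.

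The likelier bias is against the tool, so a positive finding would not be undermined in that case. This is right about direction, but a bias that can hide a real benefit is still worth removing, and the opposite sign is not excluded.

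A reader might go further and set two pilot figures against each other: tool summaries "were available to receiving teams closer to patient release (2.3 versus 45.0 hours"), and a composite that rose from 23% to 83%. If 2.3 hours were a median delay after transfer on this clock, fewer than half the summaries could have been available at transfer, which would conflict with 83%. The documents do not support that inference. They do not name the statistic behind 2.3 hours, say that it falls after transfer, or say that both figures come from the same summaries and definitions. No cap on the composite, and no size for the effect of the clock, can be drawn from the pilot.

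**Conclusion.** The point holds for the timeliness outcome as written. It times different, non-equivalent events for the two methods, neither event is availability, and the mismatch follows period closely because method does. The likelier effect is to understate the tool's benefit. The reverse requires last edits to precede viewability by more than dictation's own transcription-to-viewing delay on average.

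For the primary composite the point is conditional on its availability item using the same timestamps. A reader might infer that half of the primary outcome is measured differently before and after implementation. Table 1's label makes that possible, but the article does not say it.

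The size cannot be fixed from the documents. The figures in the working rest on assumed misclassification of 5% to 30% and full use of the tool after implementation, whereas uptake is itself to be measured. The sample size statement is correct on its own terms.

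**What to change.** In the Outcome Measures overview, Table 1 and Timeliness of Information, define one event for both methods: the time the clinician-approved summary was first viewable to the accepting team in the CIS. Use it for timeliness in hours and for the primary's availability condition, and say explicitly that both rest on it. Report the present transcription and last-edit times as a sensitivity analysis.

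If that timestamp cannot be retrieved for one method, use the closest event common to both, clinician approval, and state the expected direction of the remaining bias.

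The cost is one further electronic timestamp for 4 hospitals × 12 months × 24 = 1152 sampled summaries, plus the wording change. The documents do not say whether the system holds that timestamp, so this should be checked first. The Results section reports that abstraction was still underway, so the definition could be settled before analysis.
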